## 10. Other concomitant medication

All other concomitant medicines as per the discretion of the investigator will continue except those that are contraindicated as per product fact sheet.

## 11. Adverse Events

All adverse events whether *expected* (as stated in the proposed product fact sheet) or *unexpected* (those not mentioned in the product fact sheet) reported by patients or observed must be recorded in the CRFs with information about severity i.e. whether

- Mild: no significant interference with usual activities;
- Moderate: significant interference with usual activities or;
- Severe: prevents usual activities, date of onset duration and action taken regarding study drug.

Relation of adverse events to study medication will be described as unrelated, probable or possible.

- Unrelated: a reaction that does not follow a reasonable temporal sequence from the administration of the medicine; is not known adverse reaction pattern of the suspected medicine; could have been produced by the patients clinical state, inter current illness, trauma, accidents etc.
- Probable: A reaction that follows the reasonable temporal sequence from administration of medicine; that follow as a known or expected response pattern to the suspected medicine; and that could not be reasonably explained by the known characteristics of the patient's clinical state
- Possible: reaction that follows the reasonable temporal sequence from administration of medicine; that follows as a know or expected response pattern to the suspected medicine; but that could readily have been produced by a number of other factors including the patients clinical state or other modes of therapy administered to the patients.

Any serious adverse effects must be notified immediately by telephone to the study monitor and subsequently in writing as specified later in this section.

A serious event or reaction (SAE) is any unto odd medical occurrence that at any dose:

- Results in death
- Is life threatening
- Requires inpatient hospitalization or prolongation of existing hospitalization
- Results in persistent or significant disability/incapacity, or
- Is a congenital anomaly/birth defect

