### 3.2 Secondary Objectives

To access the safety and tolerability of Indapamide S.R. 1.5 mg + Amlodipine 5 mg

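### Section 11's causality scale has no drug-related category for a well-timed reaction that lacks a known or expected pattern

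*Protocol*

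**What the plan says.** Section 11 (Adverse Events) sets a closed scale of three grades: "Relation of adverse events to study medication will be described as unrelated, probable or possible". The definitions then run as follows.

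- **Probable** needs plausible timing and a reaction "that follow as a known or expected response pattern to the suspected medicine; and that could not be reasonably explained" by the patient's condition.
- **Possible** needs plausible timing and a reaction "that follows as a know or expected response pattern to the suspected medicine; but that could readily have been produced" by other factors, such as the patient's condition or other treatment.
- **Unrelated** combines implausible timing with two further features: the event "is not known adverse reaction pattern of the suspected medicine; could have been produced by the patients clinical state" or by other outside causes.

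The same section requires unexpected events, which are "those not mentioned in the product fact sheet", to be recorded alongside expected ones. The only secondary objective (section 3.2) is a safety one: "To access the safety and tolerability of Indapamide S.R. 1.5 mg + Amlodipine 5 mg". Section 16.2 measures it through the side-effect profile. Section 4.1 describes an open, non-comparative study, and section 2 presents the combination as new to India.

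**The concern.** Probable and Possible differ only in whether something else could explain the event. The pattern condition is the same in both, and absence of a known pattern is mentioned only under Unrelated. So the section asks investigators to record reactions outside the recognised profile, but offers no drug-related grade for one that fits no pattern.

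This matters more here than in a controlled trial. With no comparator arm, an excess of a new event cannot show up as a difference between groups. Any statement that an event is due to the drug rests on the investigator's individual judgement, and the scale rules out that judgement for reactions not previously described. What is at stake is the drug-related part of the safety description of a new fixed combination.

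**Working it through.** The protocol gives no figure to reproduce, so the check is a logical one. Describe each event by three yes/no attributes taken from the section 11 definitions:

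- T: the timing is plausible.
- K: the pattern is known or expected.
- A: another explanation is available.

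Then:

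- Probable = T and K and not A
- Possible = T and K and A
- Unrelated is built from not T, not K and A. The text separates these with semicolons and does not say whether all are needed or one is enough, so both readings are tried.

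| T | K | A | Related grade | Unrelated if all needed | Unrelated if one suffices |
|---|---|---|---|---|---|
| yes | yes | no | Probable | no | no |
| yes | yes | yes | Possible | no | yes |
| yes | no | no | none | no | yes |
| yes | no | yes | none | no | yes |
| no | yes | no | none | no | yes |
| no | yes | yes | none | no | yes |
| no | no | no | none | no | yes |
| no | no | yes | none | yes | yes |

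Results:

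1. Four of the eight combinations lack a recognised pattern. None of the four is Probable or Possible, on either reading of Unrelated.
2. If all criteria are needed for Unrelated, 3 of 8 combinations have a category (one each for Probable, Possible and Unrelated) and 8 − 3 = 5 have none. The critical case is among those without: plausible timing, no known pattern, no other cause.
3. If one criterion is enough, all 8 combinations have a category, but the critical case is then Unrelated. In addition, an event with plausible timing, a recognised pattern and another possible cause is both Possible and Unrelated.

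The conclusion about novel reactions therefore does not depend on how Unrelated is read. Only the destination of the event does. Neither reading gives a scale in which every event has exactly one place.

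**The case against.** The strongest reply is that the consequences are limited, and much of it stands.

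- **Unexpected is not the same as having no known pattern.** A reader might infer that every reaction missing from the product fact sheet is barred from the related grades, so that the count of related unexpected reactions must be zero. The text does not support that. Section 11 ties *expected* to the fact sheet, but the causality criterion also accepts a *known* pattern, and nothing ties that word to the fact sheet. An unlisted event that fits the known pharmacology of a component could still be Possible or Probable. What remains excluded is the narrower set with no recognised pattern at all.
- **Such events are not necessarily filed as Unrelated.** That follows only if one Unrelated criterion is enough. Otherwise the event has no category, and what an investigator would then choose is conjecture.
- **The events are not lost.** Section 11 requires all adverse events to be recorded. Its reporting subsection requires serious events to be notified whatever their presumed cause. Section 19 allows termination for safety issues without reference to a causality grade.
- **The side-effect profile need not be restricted to related events.** Nothing in section 16.2 restricts it, and which table leads is a matter for the statistical analysis plan.
- **The set may be small.** Section 2 says both components have been on the Indian market for about 20 years and are already taken together.

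None of this opens a related grade to a truly novel reaction. Nor can a later analysis plan repair it: the investigator assigns causality under the protocol's definitions, and a judgement that the scale did not allow cannot be recovered afterwards.

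**Conclusion.** The defect holds and should be fixed. Under the current section 11, a reaction with plausible timing but no known or expected pattern for either component cannot be graded as drug-related. It is left without a category or becomes Unrelated, depending on how that definition is read.

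The effect is on attribution only: any tabulation of drug-related events would under-count novel reactions. The size of the under-count cannot be given, because the protocol states no expected rate for them. The conclusion rests on reading the pattern condition as required in both related grades, which is how the sentences are built (joined by *and* in Probable and by *but* in Possible). It also treats the pattern wording in the three definitions as one attribute. It does not support the wider claims that safety data would be missed or that the whole side-effect profile is biased.

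**What to change.** Reword the definitions in section 11:

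- **Unrelated:** timing not plausible, or another cause clearly established. Either one is sufficient, and the text should say so.
- **Probable:** timing plausible and no reasonable other explanation. A recognised pattern supports this grade but is not required.
- **Possible:** timing plausible, with or without another available cause, and no pattern condition. State that it takes every event that is neither Unrelated nor Probable, so that each event fits exactly one category.

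The critical case then has a related grade, and the overlap between Possible and Unrelated disappears.

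The cost is wording in section 11 and matching CRF guidance, with no change to visits, treatment or sample size. Slightly more events will be labelled possibly related. The change should be in place before the first event is assessed; otherwise judgements made on the present scale would have to be reassessed.

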#### Reporting of AEs

All serious adverse events whether considered to be associated with the study medication or not, must be reported within 24hrs, or at least on the following working day by telephone or fax ([contact]) to the sponsor. Subsequently the investigator should complete the serious adverse event form attach with the case report form and fax the same to the sponsor. The event must also be documented on the adverse event page on the case report form.

The investigator would also inform the ethics committee as soon as possible within 7 working days of it occurrence.

## **12. Ethical Requirements**

#### Informed Consent

Informed consent will be obtained from each subject. The investigator will give each subject full information about the nature, meaning and importance of the study & a description of the procedures to be followed by the subject, all in accordance with Declaration of Helsinki. They will further be given a description of any foreseeable risks and discomforts. Subjects will also be told that they have the right to opt out of the trial at anytime without having to give reasons and without prejudice to further treatment. Each subject will be given a copy of the subject information sheet and will be given sufficient time to consider the implications of the study before deciding whether or not to participate in the trial.

The Informed consent form must be signed by the subject and the investigator. At this time the subject must have the legal capacity and be able to comprehend the nature, meaning, importance and risks of the study and to make up his/her mind accordingly.

If the subject is illiterate, subject's legally acceptable representative (LAR) may understand and sign the Informed consent form.

If the subject and subjects LAR both are illiterate an impartial witness (a person, who is independent of the trial and who cannot be unfairly influenced by people involved in the trial) will attend the entire informed consent process and will read out the subject information sheet and the informed consent form in a language best known to the subject.

Signed Informed consent means the acceptance that the individual's data will be known to the Investigator, the sponsor and possibly the Regulatory Authorities.

### **13. IRB/Ethics Committee**

The study will be performed in accordance with the principles stated in the Declaration of Helsinki. Prior to study initiation, approval of the study protocol will be obtained from the IRB/EC. The opinion of the EC will be dated and given in writing. Whenever possible, the names and titles of the members attending the EC meeting should be appended. The approval must clearly identify the protocol and other documents submitted for reviews, by title and study code.

### **14. Study monitoring and supervision**

The study will be managed and supervised by the Clinical Research Department of the sponsor. The responsible people will maintain the contact with the investigator and will visit the centres at the time of study initiation, during the study period and at the end of the study. They will verify all the documents and source data pertaining to this study at the study sites.

## 15. Drug Supplies and management

The study medication, FDC of Indapamide S.R.1.5 mg + Amlodipine 5 mg is manufactured by Serdia Pharmaceuticals (India) Pvt. Ltd. will be used in the study and supplied at the site. It is manufactured as per the current cGMP norms and the product specifications and the certificate of analysis shall accompany the product. It will be supplied in the sealed aluminium strips with appropriate labels and patient numbers. The study product shall bear the label "FOR CLINICAL TRIAL USE ONLY".

At each centre the study medication inventory shall be maintained and monitored. Every dispensing and return of unused study medication shall be documented. The unused study medication will be collected back by the sponsor and will be destroyed. Appropriate documentation shall be made for the same and shall be archived.

## 16. Biometry and statistical analysis

The data of the study will be statistically analysed using SPSS version 11 statistical programme using appropriate statistical tests.

16.1 Primary evaluation criteria: The primary evaluation criterion is the efficacy of the treatment in achieving the target blood pressure control. This will be evaluated as under:

- Reduction in blood pressure from baseline to end of study
- Blood pressure control rates observed in the patient population

16.2 Secondary evaluation criteria:

Safety and tolerance of this drug treatment in terms of side effects profile.

## 17. Data Archival

Copies of the CRFs, laboratory investigation reports, and other original source data related to the study will be preserved for 15 years by the Investigator. A signed inventory of the stored data will be held by the Investigator and a copy by the sponsor. The protocol, IB, CRFs copies of regulatory permission, drug analytical data and all correspondence and reports related to the study will be retained by Serdia Pharmaceuticals (India) Pvt. Ltd. for 15 years.

## 18. Confidentiality

The identity of patients and data generated in the study will be held in strict confidence. Data will be available only to doctors/scientists/auditors involved in the study and to the Regulatory Authorities.

## 19. Early Study Termination

The study will be terminated in case of any safety issues and /or protocol violations. The study may also be discontinued at a center for reason of particularly low recruitment rate, or inadequate data recording or any other issues that may necessarily require study termination. In any case, the investigator shall keep the Ethics Committee updated on the study progress. The sponsor shall keep the regulatory authorities informed about such decisions.

## 20. Study Time Table

Scheduled Date of Start : January 2010

Scheduled Date of completion : April 2010

## 22. Study at a glance

[figure not shown]

## 23. Patient Activity Chart

| Activity                                               | Pre Selection Visit | Baseline visit, Visit 1 (D 0 ) | Follow-up visit, Visit 2 (D 15 ) | Follow-up visit, Visit 3 (D 30 ) | End of study visit, Visit 4 (D 45 ) |
|--------------------------------------------------------|---------------------|-------------------------------------------|---------------------------------------------|---------------------------------------------|------------------------------------------------|
| Informed Consent                                       | X                   | --                                        | --                                          | --                                          | --                                             |
| Blood pressure, Heart rate                             | X                   | X                                         | X                                           | X                                           | X                                              |
| Laboratory investigations                              | X                   | --                                        | --                                          | --                                          | X                                              |
| Eligibility Criteria                                   | X                   | X (based on lab reports)                  | --                                          | --                                          | --                                             |
| Demography, clinical characteristics & Medical history | X                   | --                                        | --                                          | --                                          | --                                             |
| Clinical examination                                   | --                  | X                                         | X                                           | X                                           | X                                              |
| Study medication to be provided                        | --                  | X                                         | X                                           | X                                           | --                                             |
| Dosage schedule of study medication                    | --                  | Once daily with breakfast                 | Once daily with breakfast                   | Once daily with breakfast                   | --                                             |
| Adverse events                                         | --                  | --                                        | X                                           | X                                           | X                                              |
| Treatment compliance                                   | --                  | --                                        | X                                           | X                                           | X                                              |

